## 1. INTRODUCTION

### 1.1 Background

Recent global figures from the World Health Organisation (WHO) indicate that the high prevalence of obesity is not just a problem of the industrialized countries, but also a raising concern in low and middle-income countries (LMIC), with more than 1.9 billion adults being overweight, of which 650 million obese. This increase in the prevalence of obesity also indicates that many LMIC are now confronted with a double burden of disease where both still highly prevalent communicable and rising chronic non-communicable diseases (NCDs) co-exist. In most countries in Sub-Saharan Africa (SSA), women are more likely to be obese or overweight than men. Obese (Body mass index (BMI)  $\geq 30$  kg/m^2) women have a 28-times higher risk of developing T2DM than women with a normal weight. Due to the increasing prevalence of obesity, it is expected that rates of T2DM will be also increasing among women in SSA. Obesity is particularly alarming among women of reproductive age in urban SSA, among which rates have doubled or tripled over recent years. The consequences of obesity on women of reproductive age particularly detrimental during pregnancy. Obese women are recommended to gain only 11-20 pounds during pregnancy, in contrast to 25-35 in overweight and 25-35 pounds in women with normal weight. The prevalence of maternal (pre-pregnancy or first trimester) obesity in SSA varies widely across countries from 6.5 to 50.7%, with older and multiparous women being more often affected. Women whose weight gain during the first trimester of their pregnancy is outside the recommended ranges may be more at risk for GDM, a transitory condition but associated with serious health implications for both the mothers and the offspring. Recent studies in SSA reported a pooled prevalence of T2DM in non-pregnant women of reproductive age of 7.2%. Maternal overweight or obesity before conception is associated with the onset of GDM, which prevalence is estimated to be 20.4% in Central Africa. Importantly, GDM is associated with fetal macrosomia, perinatal mortality, preeclampsia, and caesarean delivery. Studies have shown that women with a history of GDM have an increased risk of developing overt cardiovascular disease. Furthermore, children born with macrosomia are more likely to develop obesity, T2DM, early cardiovascular disease, and certain cancers later in life. With overlapping risk factors, T2DM and GDM can both be prevented by maintaining an optimal lifestyle, including adequate dietary habits and physical activity levels. A wealth of studies suggests that lifestyle modification strategies to prevent T2DM that are delivered under real-world conditions are effective for promoting weight loss, a known metabolic risk factor for T2DM. There is also solid evidence on the effects of maintaining optimal diet and exercise habits during pregnancy in the reduction of the risk of GDM, highlighting the need for comprehensive (diet and physical activity) GDM preventive packages. Akin to the recommendations to increase physical activity for preventing T2DM, women at risk for GDM are recommended to do exercise at a moderate intensity, a minimum of three times a week for 30-60 min each time. A recent study in the DRC found an overall prevalence of obesity, T2DM, and hypertension, of 4.5%, 11.7%, 18.2% respectively. Women of reproductive age are a particularly vulnerable group, and there is a need for prevention programs that address the increasing incidence of prediabetes, T2DM, and GDM.

## 1.2 Rationale

The long-standing Kin-Antwerp project, sponsored by the City of Antwerp and supervised by the Institute of Tropical Medicine Antwerp (ITM) and operationalized by Memisa Belgium, has been successfully improving the lives of diabetic patients in Kinshasa. This established project encompasses 20 healthcare centers across the city, with an operational infrastructure equipped with experienced peer educators trained in diabetes management and infrastructure for an operational database for patient's follow up. During the last evaluation of the Kin-Anvers project in February 2020, overall positive feedback was gathered from participating partners, and several strengths were identified, among others: 1) The quality of the training curriculum of peer educators coordinated by the Centre d'Éducation Diabète et Santé (CEDS), 2) The decentralized diabetic-care structure, 3) The effectiveness of the appointment and monitoring system through the 'carnets de soins', and 4) The wholesome collaboration among stakeholders in diabetic care. Some areas of improvement were also observed, namely: 1) Partial usability of the operational database of T2DM patients to extract evidence to inform improved strategies, and 2) The dissimilar (or absent) approach of strategies for diabetes prevention across primary healthcare centers.

Based on the above, and in order to increase the preventive aspects of the program, and optimize the use of the limited available resources, the study partners opted for a refocus of the program. Due to the pivotal importance of placing preventive measures to decrease disease (diabetes) burden, particularly among vulnerable populations, and alleviate the health systems, we will build on the existing infrastructure of Kin-Antwerp to develop and implement an intervention program focused on the prevention of T2DM and GDM of women of reproductive age through lifestyle modification in Kisantu, DRC (KIS-Antwerp).

As in previous collaboration, ITM's role in this research is to provide scientific research guidance and supervision while Memisa is responsible for the operationalization and implementation of the study. Important to consider, the local health authorities (health district) will also cooperate in this project, as they are responsible for the primary health care at the operational level in DRC. These entities are in charge of developing health services and promote quality of care in all health facility. Due to these facts, the collaboration and involvement of the health district management team in Kisantu is an asset to our project, mainly for the monitoring of the sustainability of the project. Specific roles of the health district team entail intervention delivery, planning of service development as well as activities and resources, development of specific instructions or strategies, staff training, management, supervision and medical audit, operations research, quality assurance, review of hospital records and coordination.

## 2. STUDY OBJECTIVES

The overall objective of KIS-Antwerp is to develop, implement, and evaluate an intervention program for the prevention of T2DM and GDM among women in Kisantu (DRC) through the promotion of a healthy lifestyle and maintenance of healthy weight. After the evaluation, the intervention program will be made available for its integration in Kisantu's health systems, from where it could be potentially adapted to other areas in the country. To achieve this overall aim, the following specific objectives are planned:

1. Development of an effective strategy based on the promotion of healthy lifestyles to reduce the incidence/prevalence of overweight and obesity among women of reproductive age in Kisantu.

2. Development of an effective strategy based on the promotion of healthy lifestyles to increase the number of women who maintained a healthy weight gain during pregnancy corresponding to their pre-pregnancy weight.

To support these objectives and tackle potential weaknesses in the health system, structural and capacity-related objectives are also envisioned:

3. Improving the usability of data capturing systems for participant's follow-up and strategy-adaptation based on data analysis.
4. Improving knowledge among healthcare providers on effective strategies for the prevention of T2DM and GDM and their risk factors.
5. Improve the technique and precision of measurements concerning health visits among healthcare providers.
6. Improving women's attendance to antenatal care and therefore have an impact on maternal and neonatal health.
7. Promote a healthy lifestyle through the support of community-based strategies.

## 2.1 Primary Outcome

The primary outcome of this study is the adherence to a healthy lifestyle measured by a validated closed-ended questionnaire adapted to the context (**Annex 1**). This questionnaire emphasizes questions regarding an optimal diet and physical activity and it has been validated for weight control in lifestyle-related disease. This questionnaire provides a final score ranging between 14-65 points. A lower score indicates poor adherence to a healthy lifestyle, while a high score indicates good adherence.

## 2.2 Secondary Outcomes

Other measurements include the anthropometry (weight, height, BMI, and waist circumference) as well as the clinical indicators of systolic blood pressure (SBP), diastolic blood pressure (DBP), and glycemic levels (this measurement will provide information on the absence or presence of pre-diabetes, T2DM, and GDM). Moreover, micronutrient adequacy will be evaluated by a dichotomous indicator of the minimum dietary diversity for women developed by the Food and Agriculture Organization of the United Nations (FAO). Also, physical activity frequency, duration, and type of physical activity will be assessed by using the International Physical Activity Questionnaire (IPAQ)-Short version.

To determine the possibility of complementing the intervention program with community based activities, close-ended Likert scale questionnaires with an agreement scale will be performed. Also, focus groups per healthcare center will be carried to understand the acceptability of community support and intervention perception.

### 3. STUDY DESIGN

#### 3.1 General study design

##### **Intervention program**

We will develop an educational-motivational-based intervention program to be provided at the healthcare center by community peer educators. The intervention program is based on the strategy for T2DM control implemented in Kinshasa (Kin-Antwerp), that will be tailored to the study participants characteristics and needs, and emphasizing the preventive component of T2DM and GDM through weight control and the promotion of a healthy lifestyle, optimal diet, and physical activity, as advised by the WHO . As behavior change is challenging and motivational components have been associated with increased effectiveness in interventions that aim to promote diet and/or physical activity , motivational components will be integrated into the intervention program as well. Also, we aim to investigate during the first year of intervention if the intervention program can be complemented with community activities, as evidence has suggested that community participation is a fundamental element for positive public health impact . If acceptable, community activities will be implemented in the second year of intervention program. The intervention program will be based on multicomponent interventions as it has been proven to be the most effective approach , mainly when targeting diet and/or physical activity . The intervention program will include the components of: Individualized education, group education, physical activity sessions, goal setting, use of pedometer, and community activities if possible.

The delivery method of the intervention program and place to be provided are the following:

- Individualized method: healthcare centers and/or home visits
- Group method: healthcare centers
- Community method: parks, community room, home (second year of intervention program, if possible)

##### **Evaluation study design**

A cluster randomized controlled trial (cRCT) with a hierarchical design will be conducted whereby 2 groups of 3 healthcare centers (in total 6 healthcare centers) will be randomized to an intervention group or comparison group. The intervention group will be provided with the intervention program based on educational + motivational strategies whereas the comparison group will be limited to a basic educational strategy only (**Figure 1**). This design allows us to provide all women with proven effective preventive strategy (education) while testing for a comprehensive approach (education + motivation). The intervention program will last 24 months, starting approximately in September 2021 until September 2023 (Timeline of the study is presented in **Annex 2**).

The intervention program components and topics covered by the intervention group entail the following: Individualized education, group activities (group education and physical activity sessions), goal setting, use of pedometer, and community activities (if possible in the second year of intervention). In contrast, the components compromised in the comparison group are limited to basic individualized education at baseline only. Further information regarding the intervention program components and topics is presented in **Annex 3**.

[figure not shown]

**Figure 1.** Study design and intervention program components

### 3.2 Baseline surveys or sub-studies (if applicable)

Not applicable.

## 4. PARTICIPANTS, POPULATION & SELECTION

### 4.1 Settings, selection & recruitment

The study will be carried out in Kisantu health district (ZS Kisantu) encompassing a total population of 202,451 inhabitants. Six healthcare centers (NKANDU 1, KINTANU ETAT, NGEBA, KAVWAYA, KINKOKA, MADIMBA) covering approximately 107,000 inhabitants and sharing an integrated strategy of focused antenatal care (ANC) have been identified as operational/interventional centers. Based on past demographics, a total of 4,200 women per year are expected to be pregnant within the 6 centers population coverage, and of those approximately 92% will attend ANC at least in one occasion. Only a modest proportion of women (25%) are expected to attend the recommended 4 visits to ANC.

Women of reproductive age (pregnant and non-pregnant) will be recruited primarily through the healthcare centers in Kisantu as women attend frequently to healthcare centers due to general consultations for ANC and post-natal care, child monitoring, vaccinations among others. Within the 6 healthcare centers previously stated, health workers will identify women meeting the study legibility criteria and provide information about the study. If not enough women could be recruited via the healthcare centers consultations, informative posters will be displayed in the waiting rooms of the healthcare centers with a contact person for further information. If such posters are necessary and plan to be implemented, the posters will be submitted to the Ethical Committee in DRC and IRB at ITM for review and approval. Also community/village leaders will be approached and asked to encourage women to participate. Women interested in participating and meeting the eligibility criteria will be provided with detailed information about the intervention program, including all the specifics of the informed consent (IC). The recruitment of participants will be performed in 1 month, August 2021.

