### 4.3 Sample size

The present study is based on a three-level hierarchical design where two groups of 3 healthcare centers (matched in population size and geographical area, urban/rural) will be randomized to the intervention and comparison group, and healthcare workers within the same cluster provide the intervention allocated to the participants

The sample size will be based on the expected differential change in the primary outcome of the study (healthy lifestyle score) determined by the questionnaire developed and validated in India by Dubasi and co-workers to assess the adherence to dietary and physical activity advice for weight control in lifestyle-related diseases. The questionnaire's total score ranges between 14-65 points, a lower score indicates poor adherence to a healthy lifestyle, while a higher score indicates good adherence.

In this cRCT, 1 group of 3 healthcare centers will be randomly allocated to the intervention group and the other group of 3 healthcare centers to the comparison group. A comparable study measuring also lifestyle behavior changes as primary outcome, and using a similar score scale has reported a differential improvement from baseline to follow-up after 35 weeks of 20% between intervention and comparison groups. Also, literature has reported intra-class correlation (ICC) coefficients for interventions concerning dietary and physical activity improvements range in between 0.007-0.3.

Based on this previous evidence and the demographics of our study setting, the following assumptions have been used to approximate a power calculation estimate. This calculation was done using STATA version 16 for a cluster-randomized design assuming a realistic number of participants sample from each healthcare center whereby the following parameters were considered:

- 48 participants per cluster (144 participants per intervention program)
- Improvement of 12% in the lifestyle questionnaire score between intervention and comparison group (+ 6 score points)
- Effect size of 0.7 (score of the average person in the experimental group is 0.7 standard deviations above the average person in the comparison group, thus surpasses the scores of 69% of the comparison group).
- ICC of 0.1
- 20% loss to follow up and no attrition expected

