#### 4.4 Randomization

We will use matched randomization to ensure that the two groups are balanced in terms of population size coverage and geographical area (urban/rural). This will be performed by manually creating 2 groups, each of 3 healthcare centers, based on their population size coverage and geographical area followed by randomly assign the intervention and comparison group to the 2 balanced groups. The randomization will be performed before the intervention begins and it will be carried out by ITM's staff.

Due to the nature of this research and the impossibility of masking the intervention program, this study will not be blinded. Anyhow, to ameliorate the risk of bias, the cluster randomization design was chosen to avoid contamination of information between the participants per healthcare center.

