#### **8.3.5 Subgroup analyses**

To explore differences in the evolution between pregnant and non-pregnant women, subgroup analysis for the primary and secondary outcomes will be performed. Other potential subgroup analysis will compromise healthy and unhealthy subgroups based on BMI, glycemia and blood pressure at baseline to assess their evolution and identify the subgroups with larger and smaller effects on the primary and some secondary outcomes.

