On average conditions, meaning 30 participants per cluster, change of 12%, ICC of 0.1 and SD of 7 points, a power of 89% would be reached. However, if one cluster withdrawal the power would decrease to 82%, borderline to detect a change with enough power. Hence, to ensure power considering a withdrawal of 1 cluster, sample size calculation presented in section 4.3 entails 40 participants per cluster plus 20% loss to follow, indicating 144 participants per arm (total of 288 participants enrolled in the study) are needed to detect a change of 12% (with ICC 0.1 and SD of 7) between the intervention and comparison group with a level of significance of 95%.

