## **Annex 9**

Profile for peer educators:

- Female
- Live in the surrounding areas of the healthcare center
- Have achieved at least 4 years of secondary school
- Flexibility to mobilize
- Proven communication skills
- Request the advice of the Health Area Development Committees (CODESA) and Zones de Santé (BCZS).

Profile for health worker:

- Female, if possible
- Work as a health professional in one of the 6 healthcare centers of the study
- Collaborate among maternity, pre-natal consultations (CPN), child monitoring or outpatient consultation
- Agree to collaborate in the study

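### No common pregnancy mix is set across the six centres and the models do not adjust for pregnancy, so chance imbalance adds avoidable noise, above all to weight, BMI and waist

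*Combined protocol and SAP*

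**What the plan says.** Section 4.1 describes a single recruitment pool: "Women of reproductive age (pregnant and non-pregnant) will be recruited primarily through the healthcare centers in Kisantu as women attend frequently to healthcare centers". It names antenatal, post-natal, child-monitoring and vaccination contacts, allows one month, and keeps posters and community leaders in reserve. Section 4.2 admits non-pregnant women and women in the first trimester. Section 4.3 fixes only the total: "48 participants per cluster (144 participants per intervention program". No section gives a target share of pregnant women, a split by service or a consecutive-enrolment rule.

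Annex 9 asks that a centre's health worker "Collaborate among maternity, pre-natal consultations (CPN), child monitoring or outpatient consultation", so the service may differ from centre to centre. Section 4.4 seeks only that "the two groups are balanced in terms of population size coverage and geographical area (urban/rural".

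Section 8.3.3 specifies a linear mixed model for repeated measurements with a random cluster effect, and 8.3.4 applies the same method to the secondary outcomes. Neither names a pregnancy covariate. Section 8.3.5 nevertheless plans a pregnancy analysis: "To explore differences in the evolution between pregnant and non-pregnant women, subgroup analysis for the primary and secondary outcomes will be performed". Pregnancy status is not among the baseline variables in Table 1 or the demographic items in 5.3, although eligibility under 4.2 cannot be judged without it.

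**The concern.** Pregnancy changes weight and waist whatever the programme does, and it can plausibly change diet and exercise answers too. If centres enrol different shares of first-trimester women, the average change differs between centres for reasons unrelated to the intervention. With three centres per arm, these differences need not cancel, and an unadjusted model leaves them in the arm contrast. The pregnant subgroup in 8.3.5 and the gestational weight-gain aim (objective 2 in section 2) also rest on a number of pregnant women that the plan never estimates.

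**Working it through.** **Plan's own power.** Inputs: a 6-point effect and one-sided 0.05 (4.3); three centres per arm; 40 evaluable per centre, "with ICC 0.1 and SD of 7" (8.4). With m evaluable women per centre, SE = 7 × √[2 × (1 + (m − 1) × 0.1) / (3m)] and power = Φ(6/SE − 1.645). For m = 40 the design effect is 4.9, SE = 7 × √(2 × 4.9/120) = 2.00 and power is 0.912. The plan states 91%. With two centres against three the formula gives 0.850, and the plan states 85%. Both reproduce.

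**Pregnant women if recruits mirror the catchment.**
- Section 4.1 expects 4,200 pregnancies a year, so 4,200 × 3/12 = 1,050 women are in the first trimester at any time.
- Assume women aged 18-49 are 18-25% of the 107,000 inhabitants. Then 1,050/(107,000 × 0.25) = 3.9% and 1,050/(107,000 × 0.18) = 5.5%.
- Of 288 women, that is 11 to 16. Per centre, 48 × 0.8 × 3.9-5.5% = 1.5 to 2.1 evaluable.
- For m = 2, SE = 7 × √(2 × 1.1/6) = 4.24 and power for 6 points within the pregnant subgroup is 0.41. A t reference with 4 degrees of freedom, reflecting six clusters, gives 0.32.
- For the pregnant versus non-pregnant difference in effect, with 2 and 38 evaluable per centre, SE = 7 × √0.9 × √[2 × (1/6 + 1/114)] = 3.93 and power for 6 points is 0.45.

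**Chance gap in pregnant share between arms.** Assume the six centre shares are drawn uniformly from 5% to 60%. The variance per centre is 0.55²/12 = 0.0252. The difference between two means of three centres has SD √(2 × 0.0252/3) = 0.130. Simulation gave a mean absolute gap of 0.104 and a 95th percentile of 0.252. A normal approximation gives 0.80 × 0.130 = 0.10 and 1.96 × 0.130 = 0.25. Halving the assumed range halves these figures.

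**Shift in the score estimate.** Assume pregnancy alters score change by 3 to 6 points (the documents give no figure).
- On average: 0.104 × 3 = 0.3 and 0.104 × 6 = 0.6 points.
- At the 95th percentile: 0.252 × 3 = 0.8 and 0.252 × 6 = 1.5 points.

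**Shift in weight.** The Table 1 footnote gives a recommended gain of 11-16 kg for a normal pre-pregnancy BMI. A 10-point gap in share is worth 1.1 to 1.6 kg, and a 25-point gap 2.8 to 4.0 kg. These are upper bounds and apply mainly to the 6-month visit, when women enrolled in the first trimester are late in pregnancy.

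**What adjustment does.** With complete data, the arm-by-visit estimate is a contrast of within-woman changes. A covariate that is constant over time cancels from those changes, so a pregnancy main effect cannot alter the estimate. In a two-time-point simulation with imbalanced pregnancy, the arm-by-time estimate was 1.50 without the main effect and 1.50 with it; adding pregnancy-by-time brought it to −0.12. In a separate simulation with a 6-point pregnancy effect on change, the interaction cut the SD of the arm-by-time estimate from 1.16 to 0.83 points. The variance removed, √(1.16² − 0.83²) = 0.81, agrees with 6 × 0.130 = 0.78 from the share calculation.

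**The case against.** The strongest reply is that this is ordinary between-centre variation, most of it already allowed for. The plan assumes a between-centre variance of 0.1 × 49 = 4.9. Under the shares assumed above, mix contributes 0.0252 × 9 = 0.23 (4.6% of that) for a 3-point effect and 0.0252 × 36 = 0.91 (18.5%) for a 6-point effect. Even added wholly on top, the SE moves from 2.00 to 2.04-2.15 and power from 91% to 90-87.5%. This stands: the primary test is not in danger. It does not answer why removable noise should stay in, and it says nothing about weight.

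Three stronger readings are tempting, and the documents do not support them.
- **Systematic bias by arm.** Nothing ties the recruiting service to the arm. Separate consent forms by arm (5.2) suggest that allocation may be known at recruitment, but no text says that recruiters would select differently because of it. The calculation above has an expected gap of zero.
- **A centre made up almost wholly of pregnant women.** Section 4.1 implies 4,200 × 0.92/12/6 = about 54 first antenatal contacts per centre in the month, in any trimester. Filling 48 places would need about 90% of them to be first-trimester, eligible and consenting. Even the assumed 60% share (29 women) is at the generous end. Nor does 4.1 say that the recruiters are the Annex 9 staff or that they stay within their own clinic.
- **A failed subgroup claim.** Section 8.3.5 is worded as exploration, so low power limits how it can be read but defeats no confirmatory result.

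**Conclusion.** The point holds as one of avoidable chance imbalance. The plan leaves the pregnancy mix open, balances on other factors and omits a pregnancy term, although it must know pregnancy status for eligibility and for 8.3.5. On the score, the expected shift is 0.3 to 0.6 points, or 0.8 to 1.5 in the worst 5% of trials, which is 5-10% and 13-25% of the 6-point target. On weight at 6 months it could reach a few kilograms. These sizes rest on the assumed 5-60% range of centre shares and the assumed 3-6 point pregnancy effect on score change; neither is in the documents. If recruits mirror the catchment, the share in every centre is small. The primary contrast is then little affected, but the pregnant subgroup is too small to read. The change is worth making because it costs almost nothing and the status cannot be recovered reliably if it is not recorded at baseline.

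**What to change.** - In Table 1 and the baseline questionnaire (5.3), record pregnancy status for every woman at enrolment.
- In 8.3.3 and 8.3.4, add baseline pregnancy status and its interaction with visit as fixed effects. State that both are included, because the main effect alone leaves the arm-by-time estimate unchanged.
- Report the pregnant share by centre and by arm with the baseline table.
- In 8.3.5, call the pregnant versus non-pregnant analysis exploratory, give the expected number of pregnant women, and present estimates with confidence intervals.

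The cost is one questionnaire item, two or three sentences and five model parameters (one main effect and four visit interactions). If few pregnant women enrol, these terms will be imprecise, but there will also be little imbalance to remove.

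A fixed quota, for example 16 of 48 places per centre, is optional and not part of this fix. It would need about 30% (16/54) of a month's first antenatal contacts to be first-trimester with no refusals. It would also raise pregnant women from roughly 4-5% to 33% of the sample, which changes the population that the primary result describes.
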